## Abstract

Transcranial direct current stimulation (tDCS) has become established as an effective therapeutic approach, employed to modulate cortical excitability in various conditions. Nonetheless, few studies have assessed the use of tDCS in improving respiratory performance both in healthy and in subjects with respiratory disfunction. This randomized double-blind placebo-controlled trial evaluated the outcomes of lung function, strength of inspiratory muscles, general strength after intervention with bilateral tDCS both in young and elderly female subjects. Eighty subjects were randomized into four groups divided by age (40 young and 40 elderly) and intervention vs. placebo. After a basal (day 1) evaluation all subjects performed two evaluation/intervention rounds with 48 to 72 h interval. Lung function evaluated with spirometry evaluation with Forced vital capacity (FVC), Forced Expiratory Volume in 1 S (FEV_1_), FEV_1_/FVC Ratio, Maximal Voluntary Ventilation (MVV); Dynamic Inspiratory muscle strength evaluated with Powerbreathe and general strength with dynamometer. This study intends to understand the behavior of respiratory muscle strength and endurance after intervention with bilateral cathodal tDCS over the primary motor cortex in healthy young and elderly subjects, as a bridge for larger studies both in healthy and rehabilitation setting.

Specifications table

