**Table utbl0001:** 

Subject area:	Neuroscience
More specific subject area:	Effects of bilateral cathodal tDCS application in muscle strength and pulmonary performance in the young and elderly population.
Name of your protocol:	Bilateral transcranial direct-current stimulation on muscle strength and respiratory endurance: randomized, placebo-controlled, double-blind trial protocol
Reagents/tools:	Bilateral tDCS: Neuromodulator from Microestim Foco Research, NKL, Santa Catarina, Brazil. Forced vital capacity (FVC), Forced Expiratory Volume in 1 S (FEV1), FEV1/FVC Ratio, Maximal Voluntary Ventilation (MVV): SPM-A spirometer CONTEC™, China Powerbreathe K5 equipment (Powerbreathe, Southam, England): S-INDEX, Flow and Volume. Handgrip strength: hydraulic dynamometer (Saehan, Beijing, China).
Experimental design:	Randomized placebo-controlled double-blind trial. Four groups (*n* = 68), test (young and elderly, *n* = 34) and placebo (young and elderly, *n* = 34). Outcome measures were evaluation of lung function, strength of inspiratory muscles, general strength. After a basal evaluation, the outcomes were tested in two separated moments before and after bilateral cathodal tDCS stimulation both comparing in the same age group and comparing elderly versus young.
Trial registration:	U1111–1310–2605, International Clinical Trial Registry Platform
Ethics:	The study was conducted in line with recommendations from the Declaration of Helsinki and received ethical approval from the Ethics Committee of the Federal University of the Amazonas, Brazil [CAAE66350622.0.0000.520, evaluation 315.763].
Value of the Protocol:	tDCS is proven to be a valuable tool in rehabilitation and performance enhancement in several areas, but with little or no work done in respiratory function or respiratory rehabilitation. The main objective is to evaluate the expected improvement of the respiratory muscle strength and resistance after intervention with bilateral tDCS over the primary motor cortex in healthy young and elderly subjects. It is a randomized, double-blinded study designed to study the possibility of using tDCS for enhance respiratory performance in healthy subjects or in rehabilitation programs after respiratory injury. We highlight the construction of the study, allowing the comparison between the response in the young and the elderly.

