### Sample size and subject recruitment

The volunteers were recruited after posting invitation posters on the campus of the Federal University of Amazonas. No compensation was offered for participation in the experiment. All the subjects were female. The rationale for this was the ease of recruiting female participants, since there are activities taking place on the university campus only for elderly female.

Were inclusion criteria for the young group – ages comprehended between 18 and 25, no medical history of cardiovascular, pulmonary or neurologic conditions affecting the respiratory tract. Regarding the elderly group the inclusion criteria were the same, except the timeframe, considering ages between 60 and 80 years of age. Exclusion criteria were subjects out of the timeframe requested by the study protocol in both groups, medical history of cardiovascular, pulmonary or neurologic conditions. Also, in the selection of volunteers for the young group, those who were at the time of their menstrual period were excluded to avoid any hormonal influence on the results.

For the sample size, inspiratory muscle strength will be used through the dynamic inspiratory pressure (*S index*). As there is no study that evaluated this type of variable associated with tDCS, we will accept a priori a Cohen's size effect *F* = 0.25 (Small Effects). For sample size, ANOVA two-way repeated measures (Between-within) was calculated. Parameters used were size effect 0.25, α = 0.05, β = 80 %, 2 groups, 2 measurements (tDCS stimuli and Sham stimuli), correction between measurements = 0.5 and correction of no-sphericity ε = 1. Accepting a possible 20 % of sample loss, a sample calculation of 40 volunteers was selected both for the elderly and young group, with a global total of 80 subjects and G power 3.1 (University of Dusseldorf, Dusseldorf, Germany) was used for calculation.

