The stratification randomization (age, BMI, FVE1 and FVC) was electronically conducted by an investigator that did not take part in the evaluation of patients of application of the tests. Electronic codes were generated to introduce in the tDCS neuromodulator ensuring the blinding of the therapist and the subject assessed (doble blind). The volunteers of this research will be randomized in four groups: 20 volunteers per group, being 20 for young interventional and young placebo, and the same for the elderly. After a basal (day 1) evaluation all subjects will be part of two evaluation/intervention rounds with 48 to 72 h interval (Fig. 1).

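### The Specifications table gives n = 68 where the rest of the article gives 80, and 40 per age group covers a loss of about 15%, not the stated 20%

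*Protocol article*

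**What the plan says.** Three places in the Protocol article agree on the number randomised:

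- Abstract: "Eighty subjects were randomized into four groups divided by age (40 young and 40 elderly".
- Sample size and subject recruitment, on the target: "Accepting a possible 20 % of sample loss, a sample calculation of 40 volunteers" in each age group, with a total of 80.
- Sample size and subject recruitment, on allocation: "20 volunteers per group, being 20 for young interventional and young placebo, and the same for the elderly".

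The experimental-design row of the Specifications table gives a different size: "Four groups (*n* = 68), test (young and elderly, *n* = 34) and placebo (young and elderly, *n* = 34". It carries no label such as required, evaluable, completed or analysed.

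The sample-size section also lists the inputs for a two-way between-within repeated-measures ANOVA in G*Power 3.1: "Parameters used were size effect 0.25, α = 0.05, β = 80 %, 2 groups, 2 measurements", followed by "correction between measurements = 0.5 and correction of no-sphericity ε = 1". The 80% printed as β is evidently the power. The number required before the allowance for loss is not printed.

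**The concern.** Two design sizes, 68 and 80, stand in the same article with nothing to connect them. A reader judging attrition, or later comparing a results paper with this protocol, needs to know what 68 counts.

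The loss allowance is a separate matter. It can be checked because every input is given. If 40 per age group does not absorb the 20% loss that it is said to absorb, the sample-size statement promises slightly more protection than the numbers give.

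**Working it through.** **Inputs**, all from Sample size and subject recruitment: f = 0.25; α = 0.05; power 0.80; k = 2 groups; m = 2 measurements; correlation ρ = 0.5; ε = 1.

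**Formula.** For the within-between interaction in G*Power's repeated-measures ANOVA, power comes from the noncentral F distribution with

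- λ = f² · N · m / (1 − ρ) = 0.0625 · N · 2 / 0.5 = 0.25 N
- df1 = (k − 1)(m − 1) = 1
- df2 = (N − k)(m − 1) = N − 2

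**Step 1: number required per age group before loss.**

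| N | λ | df | Power |
|---|---|---|---|
| 32 | 8.00 | 1, 30 | 0.781 |
| 33 | 8.25 | 1, 31 | 0.795 |
| 34 | 8.50 | 1, 32 | 0.807 |
| 40 | 10.00 | 1, 38 | 0.869 |

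The smallest N that reaches 80% is 34, or 17 per arm. The within-factor test gives the same N. The between-factor test needs 97, or 98 with equal arms, and so cannot be the origin of 40.

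**Step 2: can 40 be reproduced as 34 plus a 20% allowance?**

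- Correct inflation: 34 / (1 − 0.20) = 42.5, so 43 per age group, or 44 with equal arms. That is 86 to 88 in total.
- The common shortcut: 34 × 1.2 = 40.8, which rounds up to 41. Taken down to 40 for two arms of 20, this is a likely source of the printed figure, but the article does not say so.
- Working backwards: 40 × 0.8 = 32, so 40 would be right only if 32 were enough. At 32, power is 0.781.

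The figure of 40 is therefore not reproduced as a 20% allowance for 80% power.

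**Step 3: what 40 does cover.**

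- Largest loss that leaves 34: (40 − 34) / 40 = 15%.
- At the stated 20% loss: 32 remain, power 78.1%. Shortfall 80 − 78.1 = 1.9 points.
- Gap in numbers against a true 20% allowance: 43 − 40 = 3, or 44 − 40 = 4, per age group; 6 to 8 overall.

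**Step 4: 68 against 80.**

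- 4 × 20 = 80 and 40 + 40 = 80: the Abstract and the sample-size section agree.
- The table's parts add up (34 + 34 = 68), so this is not a simple misprint of one digit.
- 2 × 34 = 68 is also the total required before loss from Step 1. However, the table's two 34s are arm totals taken across both ages, whereas the 34 in Step 1 is an age-group total. Only the sum coincides.

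**The case against.** **The power loss is marginal.** This stands. It is 1.9 points, and it arises only if the whole 20% is lost. The article says that no earlier study informs the effect size, so f = 0.25 is a convention, and the correlation of 0.5 comes without supporting data. Uncertainty in those inputs outweighs a gap of 3 or 4 volunteers per age group. On its own, the loss allowance is a minor wording correction.

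**A reader might infer that the trial as a whole is underpowered.** The documents do not support that. The calculation applies within one age group. The first research question compares stimulation with control and is not restricted to one age. With both age groups pooled, 64 remain after a 20% loss, λ = 16, and the same formula gives about 0.976.

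**A reader might take 68 as the evaluable target, with 17 per group.** The match with 2 × 34 makes this plausible, but the table neither labels 68 nor gives 17 anywhere.

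**A reader might instead take 68 as the number left after attrition.** Analysis is described as ongoing and much of the text is in the past tense, so this cannot be excluded. Nothing in the article reports it either.

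**A reader might say that the number randomised is unclear.** That goes too far. The Abstract gives 80 explicitly and the sample-size section agrees. What is unclear is what 68 denotes.

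**The inputs themselves are open to question.** The two measurements are described in "2 groups, 2 measurements (tDCS stimuli and Sham stimuli", while elsewhere sham is a separate randomised group. The check here uses only the stated counts of groups and measurements and does not endorse that description.

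**Conclusion.** The point holds in two parts.

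The more important is the unexplained 68 in the Specifications table against 80 elsewhere. It is visible on the page and needs no reconstruction. That 68 is the requirement before loss is probable, but not established.

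The lesser is the loss allowance. Under the stated inputs, 40 per age group protects 80% power up to a 15% loss, not 20%. At 20%, power within each age group is about 78%. This rests on reading the sample size as applying separately to each age group, which is the natural reading of the section, and on the interaction (or within-factor) test with the printed inputs.

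Neither part invalidates the design. Both are figures that the plan relies on, and both can be corrected.

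**What to change.** Change wording only; enrol no one further.

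- **Sample size and subject recruitment:** state that, under the stated inputs, 40 volunteers per age group (80 in total) allow a loss of about 15%, leaving 34 evaluable within each age group, and that at a 20% loss power is about 78% per age group.
- **Specifications table:** give 80 as the number randomised (20 per group). Then either define what 68 denotes (for example, the number required before loss, if the sponsor confirms it) or remove it.

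The cost is a short correction to the text and a slightly less favourable stated allowance. Recruitment, allocation and analysis are unaffected.

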### Step-by-step study design

The study is designed as an experimental and double blind randomized, summarized in Fig. 1.

### Day 1

All volunteers were evaluated initially for the presence of any exclusion criteria. After, a social demographic and anthropometric evaluation was conducted. Also, the patient's relevant medical history was recorded.

All subjects underwent baseline spirometry under controlled environmental conditions. The patient was seated and instructed to perform normal ventilations for 5 s, after a therapist command a slow expiration, followed by inspiration and forced expiration. For all participants, the device estimated a value of FVC and FEV_1_ by predicted values. A minimum of 3 and a maximum of 8 maneuvers were performed. At least 3 of these maneuvers would have to be acceptable and reproducible. Thus, differences greater than 10 % in the highest values of CVF or FEV_1_ were not admitted. The highest value of the series was chosen for both parameters in the study. The test would be stopped or restarted in the event of adverse effects such as cough or lipothymia.

### Day 2

All subjects were evaluated, within 24 h from day 1 evaluation, prior to any intervention, in quiet and temperature regulated conditions, with:-Handgrip strength. The volunteers were seated with their feet well supported, with the elbow at 90° stabilized by the evaluator at the time of the measurement. The test was performed for 3 s, followed by a 1-minute break, with repetition of the intervention for two more rounds. The highest values of the 3 rounds were picked for the study.-Spirometry evaluation with evaluation of the MVV. The patient was seated and was instructed to inhale and exhale quickly and deeply for 12 s. Up to 5 measurements were taken, choosing the one with the highest peak, as long as the variation was not greater than 10 %.-Evaluation of dynamic inspiratory strength with Powerbreathe (Powerbreathe, Southam, England). With the subject seated and using a nose clip, the patient is instructed to inhale quickly and deeply through the mouthpiece with slow exhalation to the limit achieved. Followed by pause and repetition of the movement, The volunteers performed a warm-up of 5 inhalations before the assessment, which went up to a maximum of ten repetitions (Silva et al., 2018). The chosen value would be the maximum among the repetitions.

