#### Post – intervention evaluation

-After the intervention with tDCS the patients repeated all the tests performed prior to intervention in the same technical and environmental conditions.

### Day 3

The evaluation in day 2 was conducted 48 to 72 h after the day 2 assessment. The environmental conditions were similar.

The pre and post intervention test were the same and conducted as described.

Regarding the intervention with tDCS the electrodes switched position with the anode being placed at C3 and C4 motor regions bilaterally and the cathode over the supraorbital region, also bilaterally. The intervention was then performed with the same parameters described for day 2 evaluation.

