### Statistical analysis

The data will be expressed as mean and standard deviation of the mean, median and interquartiles, and percentage. Initially, normality will be tested using the Shapiro Wilk test and homogeneity using Levene's test. For mean analysis, the unpaired *t*-test or Mann-Whitney test will be used. For the evaluation of the intervention, ANOVA two-way (between-within) *post hoc* Bonferroni test will be used. If normal values are not present, the Kruskal-Walli's test will be performed for unpaired values and the Friedman test for paired data, with Bonferroni correction for the *p*-value. Effect size calculation will be done using the G*Power 3.1 software, and statistical analysis will be conducted using the JAMOVI software (Jamovi project, Australia) and GraphPad Prism 8.0 (GraphPad, USA). Significant values accepted as *p* < 0.05

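### The stated two-way ANOVA, read as arm by pre/post, uses the pre-stimulation value inefficiently and leaves out BMI, FEV1 and FVC, on which randomisation was stratified; this costs precision but causes no bias

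*Protocol article*

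**What the plan says.** - **Randomisation** (Sample size and subject recruitment): "The stratification randomization (age, BMI, FVE1 and FVC) was electronically conducted by an investigator". There are four groups of 20, active and sham within young and within elderly.
- **Measurements.** On Day 2, "All subjects were evaluated, within 24 h from day 1 evaluation, prior to any intervention". Then, "After the intervention with tDCS the patients repeated all the tests performed prior to intervention". For Day 3, "The pre and post intervention test were the same and conducted as described". The specifications table says that "the outcomes were tested in two separated moments before and after bilateral cathodal tDCS stimulation".
- **Model** (Statistical analysis): "For the evaluation of the intervention, ANOVA two-way (between-within") with Bonferroni post hoc tests. If data are not normal, the Kruskal-Wallis "test will be performed for unpaired values and the Friedman test for paired data, with Bonferroni correction". Protocol validation names the ANOVA again. Neither section mentions a covariate.
- **Sample size.** The endpoint is the S index ("inspiratory muscle strength will be used through the dynamic inspiratory pressure"). The inputs are f = 0.25, alpha 0.05, power 80%, two groups, two measurements, correlation 0.5 and 20% loss. The result is 40 per age group. The specifications table gives 68 subjects in all, which is 34 per age group if split equally.

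**The concern.** With two arms and a pre/post factor, the arm-by-time interaction is the same test as a two-sample t-test on post minus pre. It forces the slope of post on pre to be 1. ANCOVA estimates that slope and has a smaller residual variance whenever the correlation is below 1. Stratification factors that predict the outcome beyond the pre value would normally also enter the model. If they do not, the standard error does not reflect the balance that the stratification bought. The named non-parametric tests have no place for a covariate either.

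With 20 subjects per arm in each age group, precision is scarce, and all the variables needed are already collected.

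**Working it through.** **Inputs from the article:** f = 0.25, rho = 0.5, k = 2 groups, m = 2 measurements, alpha = 0.05, sphericity correction 1, 20 per arm per age group. Correlations other than 0.5 are assumptions, shown as a range.

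**1. The plan's own figure.** For the within-between interaction, lambda = f² × N × m / (1 − rho), with 1 and N − 2 degrees of freedom.
- N = 34: lambda = 0.0625 × 34 × 2 / 0.5 = 8.5, power 0.807.
- N = 32: power 0.781. So 34 is the smallest N that reaches 80%, in line with 68 over two age groups.
- 34 × 1.2 = 40.8, close to the stated 40.
- N = 40: lambda = 10, power 0.869.

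The sample size therefore reproduces as an arm-by-pre/post interaction within one age group.

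**2. What f = 0.25 means.** In a 2 × 2 layout with cell effects of ±f, the arm difference in change is 4f = 1.0 SD. The variance of a change is 2(1 − rho) = 1.0 at rho = 0.5. Check at N = 34: lambda = (N/4) × 1.0² / 1.0 = 8.5, as in step 1.

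**3. ANCOVA on the pre value.** The residual variance is 1 − rho². Relative to change scores this is (1 − rho²) / [2(1 − rho)] = (1 + rho)/2. At rho = 0.5 the ratio is 0.75, so the standard error falls by 1 − √0.75 = 13.4%.
- N = 34: lambda = 8.5 / 0.75 = 11.33 on 31 df, power 0.903.
- N = 40: lambda = 10 / 0.75 = 13.33 on 37 df, power 0.945 (simulation with 4,000 runs: 0.938).
- N for 80% power falls from 34 to 26.

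**4. Higher correlations**, with the effect rescaled so that the ANOVA keeps power 0.807 at N = 34:

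| rho | variance ratio | SE reduction | ANCOVA power, N = 34 |
|---|---|---|---|
| 0.5 | 0.75 | 13.4% | 0.903 |
| 0.7 | 0.85 | 7.8% | 0.865 |
| 0.8 | 0.90 | 5.1% | 0.845 |
| 0.9 | 0.95 | 2.5% | 0.826 |

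**5. Cost of further covariates.** The worst case is three extra covariates that carry no information. Simulated power within one age group at N = 34 (4,000 runs):

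| rho | ANOVA | ANCOVA, pre value | ANCOVA, pre value + 3 |
|---|---|---|---|
| 0.5 | 0.80 | 0.89 | 0.86 |
| 0.8 | 0.81 | 0.84 | 0.80 |
| 0.9 | 0.81 | 0.82 | 0.77 |

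Pooled over 80 subjects, with arm, age group and their interaction in the model (3,000 runs, effect set so that ANOVA power is about 0.70):

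| rho | ANOVA | ANCOVA, pre value | ANCOVA, pre value + 3 |
|---|---|---|---|
| 0.5 | 0.71 | 0.81 | 0.80 |
| 0.8 | 0.70 | 0.74 | 0.73 |
| 0.9 | 0.69 | 0.72 | 0.70 |

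So useless covariates can cost more than the pre value gains when one age group is analysed alone and rho is high. In the pooled model they do no material harm.

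**The case against.** The stated ANOVA is valid and unbiased, it matches the sample-size method, and on the plan's own inputs it already exceeds 80% power. All of that stands. Four stronger readings are tempting, and the article does not support them.

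- *That the model adjusts for nothing.* Under the pre/post reading the pre value is in the model, and age group is part of the four-group structure. What is left out is BMI, FEV1, FVC and any finer age stratum.
- *That omitting the stratification factors must inflate the standard error.* A stable trait that shifts pre and post equally cancels in the change. These factors help only if they predict change or, in ANCOVA, the post value given the pre value. The article gives no such correlations, so no gain can be credited to them.
- *That adjustment is free.* Step 5 shows that it is not, within one age group at high correlation.
- *That the trial is underpowered without ANCOVA.* This follows only from an effect smaller than the plan's 1.0 SD difference in change.

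The correlation of 0.5 is also a planning input, not an estimate. Pre and post are maximal efforts in the same session, so a higher value is plausible and the gain may be modest.

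Two further objections do not remove the point. An unseen analysis plan might list covariates, but the article names its model twice, and the point concerns that model. The article also says that analysis is under way. That limits how the change may be made, not whether it is an improvement.

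**Conclusion.** The point holds as a cheap improvement, not as an error that threatens validity. The stated analysis gives up efficiency by fixing the slope on the pre value at 1, and it omits three of the stratification factors.

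- **Size:** at the plan's f = 0.25 and rho = 0.5, power per age group goes from 0.81 to 0.90 (N = 34) and from 0.87 to 0.94 (N = 40). The variance gain is 25% at rho = 0.5, and 10% or 5% at the assumed values 0.8 or 0.9.
- **What it rests on:** equal pre and post variances, a linear relation between them, and a within factor that is pre/post. The sample-size paragraph instead labels the two measurements as active and sham stimulation, which does not fit parallel arms and leaves the within factor unclear. If it is not pre/post, the pre value may not be used at all and the loss would be larger.
- **Not quantified:** any gain from BMI, FEV1 and FVC beyond the pre value.

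**What to change.** State as the primary analysis, separately for each session, an ANCOVA of the post-stimulation value on arm, age group, arm by age group and that session's pre-stimulation value, pooled over the 80 subjects. Enter the stratification factors in the form used to stratify. Report the adjusted arm difference with its 95% CI, and keep the two-way ANOVA as a sensitivity analysis. State also that the within factor of that ANOVA is pre/post.

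**Cost:** wording and a few degrees of freedom; no new data. With 80 subjects the core model has five parameters (intercept, arm, age group, interaction, pre value), leaving 75 df. Three single-df terms for BMI, FEV1 and FVC leave 72. In analyses within one age group the extra covariates may cost a little power when the correlation is high, so the pooled model should be the primary one.

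**Timing:** because analysis is already under way, the change must be fixed and dated before unblinded results are seen. Otherwise it should be reported as post hoc beside the stated ANOVA.
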